### 2.3. Sampling and Recruitment

We conducted formative research (Figure S2) to prepare for the implementation of our intervention. We previously described how we estimated the sample size using the Lynch formula [27]. The target population was all the public school children in Metro Manila, where in School Year 2014–2015 a total of 2,059,447 public school children (1,373,852 elementary and 685,595 secondary school children) were enrolled [23]. We inflated the sample by 30% and 45% to account for nonresponse and refusal, respectively, and then inflated the sample by another 5% to account for differences in schools’ enrollment sizes. The target sample size was N = 760; we enrolled 756 students at baseline and 703 students at the 8-month follow-up (retention rate: 86%) (Figure 3).

We selected schools located in Manila, Navotas, and Quezon City (Figure 4) because they were geographically and demographically representative of cities in Metro Manila. We recruited the school principals from the 15 public schools that participated in our previous observational study [27]. We used convenience, rather than probabilistic, sampling, choosing to revisit the same 15 schools because of existing relationships of trust and cooperation with school principals and personnel. These factors can facilitate communication and collaboration, which were crucial because we aimed to maintain a long-term working relationship with schools in spite of our limited resources in time, personnel, and materials. We previously described our multi-stage cluster sampling strategy [27]. Based on the school’s enrollment size, 1–2 class sections were selected to obtain a target sample of ~50 students per school. We recruited entire class sections as a whole rather than groups of students from multiple class sections so as not to interrupt on-going classroom instruction with our research activities. We decided not to re-recruit the students from our previous observational study as a new school year had begun, resulting in students advancing up to the next grade level (e.g., from grade 5 to 6) and moving to different class sections, as well as some students transferring to different schools that were not involved in our study. No monetary reimbursement was offered to school principals, and all schools were compensated (Table S6) with printed research portfolios, certificates of appreciation, classroom viewings of an educational film promoting handwashing, and hand hygiene gel.

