We will examine the role of missing data in the interpretation of findings. If we find no statistically significant difference between children who were missing data and children who were not missing data for key outcomes, then we will conclude that data were missing at random (MAR), though not missing completely at random (MCAR). MAR means that all data, within groups defined by the observed data, had an equal chance of being missing, and that the reason why data were missing is due to a known characteristic of the data themselves [43]. In our study, the possible reasons for MAR will likely be: nonresponse (some children did not answer all of the questions in the questionnaire) or loss to follow-up due to school absence or discontinued school enrollment because of drop-out, graduation, or relocation. On the other hand, MCAR will less likely be found in our study because it means that all data had an equal chance of being missing and that the reason why data were missing is not due to the data themselves [43]. In field research, this may be an unrealistic occurrence. We will consider using multiple imputation (MI) or full information maximum likelihood (FIML) to handle MAR data. An advantage of FIML is that it uses all available data provided by a given study participant. We will use Stata, version 15 (StataCorp., College Station, TX, USA), for all data analyses.

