Our study included intervention components (e.g., health education, poster-making and restroom cleaning contests, promotion of hygiene practices through behavioral reinforcement) that are likely to be operationalized at scale in similar high-risk, low-resource settings in LMICs because they were feasible, acceptable, and affordable. Our study will support using best practices in public health promotion and enhancing local research capacity. We provided local researchers with training about: community health, population-based research, and participatory research methods; assessments of child growth and cognitive development; use of noninvasive markers to evaluate hydration status.

The interpretation of our study findings will likely be limited because of bias due to the non-random recruitment of schools and non-random sampling of children, and the lack of randomization when we assigned school clusters to control or intervention arms. We used outcome measures that could increase the risk of bias by misclassifying children or not controlling for confounding. We used self-reported outcome measures to assess food insecurity and socioeconomic status. We used urine test strips to assess dehydration. However, we did not corroborate or triangulate findings with other sources of data. It is also possible that our assessment of health literacy via questionnaire would introduce bias. We will need to account for many missing responses due to children dropping out of our study because they graduated and/or transferred to a different school. We collected data on many outcomes and will likely run the risk of seeing a “multiple comparisons effect”. This may occur because as the number of outcome measurements increases, so does the tendency of seeing a false-positive [48].

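### Section 2.8 concludes that data are MAR and not MCAR from a non-significant comparison, which by its own definitions is the pattern MCAR predicts and cannot establish MAR

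*Protocol article*

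**What the plan says.** The second paragraph of section 2.8 states a condition and a conclusion. The condition is "If we find no statistically significant difference between children who were missing data and children who were not missing data for key outcomes". The conclusion is "then we will conclude that data were missing at random (MAR), though not missing completely at random (MCAR").

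The same paragraph defines both mechanisms. On MAR: "MAR means that all data, within groups defined by the observed data, had an equal chance of being missing", and "the reason why data were missing is due to a known characteristic of the data themselves". On MCAR: "all data had an equal chance of being missing and that the reason why data were missing is not due to the data themselves". It expects MAR because of unanswered questions, absence, drop-out, graduation and relocation, and regards MCAR as probably unrealistic in field research.

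On handling it says: "We will consider using multiple imputation (MI) or full information maximum likelihood (FIML) to handle MAR data". It does not say what follows if the comparison is significant.

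On the amount of loss, section 2.3 reports: "we enrolled 756 students at baseline and 703 students at the 8-month follow-up (retention rate: 86" per cent). The Discussion adds: "We will need to account for many missing responses due to children dropping out of our study".

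**The concern.** The rule attaches a label to a test result that does not support it. It treats failure to find a difference as positive evidence for MAR and, at the same time, as grounds to exclude MCAR. Neither step follows. The article presents this as a decision rule that will be applied, so it is not a detail left to an analysis plan.

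Two things are at stake. First, a non-significant result could be reported as having established the assumption under which imputation or FIML is valid, when missingness might depend on unobserved outcomes. Second, the text ties imputation and FIML to the MAR label, and the only test result said to lead to that label is a non-significant one. The situation in which conditioning on observed data matters most, a clear difference on observed variables, is left without any stated handling.

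The article offers itself as a blueprint for other trials, so the rule may be copied.

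**Working it through.** The plan gives no figure on this point to reproduce. The check has three parts.

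**1. The rule against the article's own definitions (section 2.8)**

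| Mechanism as defined there | What a comparison of children with and without missing data should show | What the rule concludes from that |
|---|---|---|
| MCAR: equal chance for all, unrelated to the data | No systematic difference | MAR, not MCAR |
| MAR: equal chance only within groups defined by observed data; due to a known characteristic | A difference on that characteristic | Nothing stated |
| Not at random: depends on unobserved values | A difference or none, depending on how the unobserved values relate to what is compared | MAR, not MCAR, if no difference is found |

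The follow-up outcomes of children lost to follow-up are unobserved. Only baseline or other recorded values can be compared, so the comparison carries no direct information on the MAR versus not-at-random question.

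**2. Power of the comparison**

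Inputs from section 2.3: 756 enrolled, 703 followed up, stated retention 86%. The counts and the percentage disagree: 703/756 = 93.0%, so 756 − 703 = 53 missing, whereas 0.86 × 756 ≈ 650 retained, so 106 missing. Both are used. Assumptions not in the article: two-sided 5% level, 80% power, children treated as independent. The multiplier is 1.96 + 0.84 = 2.80.

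Detectable difference (SD) = 2.80 × √(1/n missing + 1/n observed)

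- 53 against 703: 2.80 × √(1/53 + 1/703) = 2.80 × 0.1424 = 0.40 SD
- 106 against 650: 2.80 × √(1/106 + 1/650) = 2.80 × 0.1047 = 0.29 SD

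Power for smaller differences:

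| True difference | 53 missing | 106 missing |
|---|---|---|
| 0.2 SD | 29% | 48% |
| 0.3 SD | 56% | 82% |

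**3. How often the rule would give the label "MAR, not MCAR"**

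A simulation used 756 children, 4,000 runs, a baseline covariate correlated 0.5 with the outcome, and a t-test on the covariate between children with and without the outcome. Missingness was logistic in the covariate (slope 1.0 for strong, 0.3 for weak dependence) or, for not-at-random, in the part of the outcome that the covariate does not explain (slope 1.0). The correlation and slopes are assumptions. In the 14% column, the strong MAR and not-at-random runs had about 13% missing.

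| True mechanism | Non-significant, 7% missing | Non-significant, 14% missing |
|---|---|---|
| MCAR | 95% | 95% |
| Strong MAR | 0% | 0% |
| Weak MAR | 46% | 19% |
| Not at random, unrelated to the covariate | 95% | 94% |

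Under these assumptions the label goes almost always to MCAR data and to this form of not-at-random data, and never to data with strong MAR.

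**The case against.** The strongest defence has four parts.

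*The rule may be an overclaim, not a reversal.* The comparison may be meant as a rough check that missingness is unrelated to key outcomes, with MCAR dismissed beforehand as unrealistic. That is a fair reading of the intent. It does not rescue the sentence, which still draws a conclusion about the mechanism from a non-significant test.

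*Imputation and FIML are not forbidden after a significant result.* A reader might infer that they are switched off exactly when missingness is related to the data. The text does not say so. That branch is absent, not prohibited; MAR is also expected on substantive grounds; and weak dependence could go undetected, in which case these methods would still be considered. What stands is that the article does not commit to them in either case.

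*Other protection exists.* A reader might infer that a biased complete-case analysis is all that remains. No section plans one. Section 2.8.2 commits to generalized linear mixed models for the effect of each intervention, with no missingness test. If fitted by likelihood to all available measurements, these give some protection under MAR. The limit is that their fitting is not described, and the t-tests, Poisson and logistic models in the same section carry no such general protection.

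*No harm to the trial result has been shown.* This stands. The 0.40 and 0.29 SD figures describe the power of the missingness test, not bias between arms. In the simulation, ignoring incomplete children shifted one overall mean by −0.03 SD (7% missing) and −0.06 SD (about 13%) under strong MAR, which a FIML-type estimate removed. Under the not-at-random case the shift was −0.06 and −0.10 SD with either method. Bias in an arm difference would need missingness to act differently by arm, which was not modelled. How school clustering changes the power of the test was not shown either.

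The Discussion's remark on many missing responses may also refer largely to the 17-month household questionnaire: the notes to Figure 2 and Table 2 mention graduation and transfer there, not at the 8-month outcomes.

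**Conclusion.** The point holds: the classification rule in section 2.8 is wrong as written. It conflicts with the definitions beside it, it treats non-significance as evidence, and it claims to settle a question that observed data cannot settle. The conflict with the definitions rests on the text alone. The detectable differences rest on an assumed two-sided 5% level and independent children, with the range reflecting the article's inconsistent retention figures. The misclassification rates rest on the simulation assumptions.

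The size of any effect on the arm comparisons is not established. A reader might also count the lack of a not-at-random sensitivity analysis as part of the error. It is not, because an article commonly leaves that to the full analysis plan. This is something that should be fixed, not a defect that by itself invalidates the planned analysis.

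**What to change.** - Delete the significance test as a way of classifying the missing-data mechanism.
- State MAR given arm, school, grade, age, sex and baseline outcome as a working assumption that the data cannot verify.
- Make the likelihood-based mixed model on all available data, or multiple imputation that respects school clustering, the main analysis whatever any comparison shows.
- Report the amount of missing data by arm and grade, and the characteristics associated with it, descriptively.
- As a useful addition, vary the assumption in a not-at-random sensitivity analysis.

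The cost is a few sentences in section 2.8 and a modest amount of extra analysis. No new data are needed.

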#### 2.8.1. Descriptive Analyses

We will conduct descriptive analyses, pre- and post-intervention, to measure study participation, demographic characteristics, and outcomes of interest. We will report baseline characteristics for all five study arms. For each primary and secondary outcome, we will report results (e.g., means, proportions) for each arm, including the estimated effect size and precision. To describe exposure to inadequate WaSH at school and at home, we will measure frequencies and interquartile ranges (IQRs) relevant to schools’ and homes’ WaSH facilities. Data from school inspections will be summarized at the school-level by measuring the mean scores of individual facility inspections. To describe outcomes of poor health literacy, poor handwashing, and malnutrition, we will measure prevalence rates using contingency tables with estimates of standard error (SE) and precision.

#### 2.8.2. Inferential Statistical Analyses

To address study aims 1 and 3 (Figure 2), we will compare the study arms, using two-sided tests for primary outcomes. For continuous variables, we will use the *t*-test to calculate the mean weight differences between the control and intervention arms. For binary variables, we will use Poisson regression to compare the control and intervention arms according to their relative risk (RR). We will use multiple logistic regression models to analyze exposure-response: g = (E[Ai]) = β0 + β1Bi + γCi, where Ai is the primary outcome of interest, g( )  is the appropriate link function (identity for height and weight, logistic for stunting and poor health literacy), Bi is the continuous exposure of interest, and Ci is the vector of confounders. We describe proposed models in Box S2 and will describe full models in a forthcoming paper [25].

To assess risk factors of health, health literacy, and handwashing outcomes, we will use multiple logistic regression models that account for school-level clustering, estimate precision with 95% confidence intervals (CI), and *p*-values, and produce adjusted odds ratios (aORs). Clustering by school takes into account potential intragroup correlation among children from the same school and enables us to adjust the SE of estimates. aORs control for possible confounders (e.g., children’s age and sex, parent’s educational background and employment status, presence of toilet and handwashing basin inside home, household food insecurity). We will use confounders to calculate an adjusted effect estimate to account for baseline differences between the control and intervention arms. We will use three multiple logistic regression models (Box S2): (1) model A for poor hygiene literacy only, poor handwashing literacy only, and both poor hygiene literacy and poor handwashing literacy; (2) model B for malnutrition, i.e., stunting only, undernutrition only, and overnutrition only; and (3) model C for poor health status only, extreme hunger only, and both poor health status and extreme hunger.

We will use generalized linear mixed models (GLMMs), which are appropriate for longitudinal data, to determine if the intervention was effective in improving our outcomes of interest. GLMMs are useful for measuring intervention impacts in complex datasets, i.e., when different types of variables (e.g., binary, continuous) are assessed at different time periods, particularly when assessments are made at the group- rather than individual-level. We will use GLMMs to estimate the effect of each intervention compared to the control group. To measure the intervention’s impact, we will estimate differences between pre- and post-intervention outcomes.

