### 2.5. Data Collection

#### 2.5.1. Assessing Primary Intervention Outcomes

First we assessed children’s health literacy, measured by two continuous variables (hygiene literacy and handwashing literacy scores) via questionnaire (Tables S3 and S4). Second we assessed child growth, measured by continuous variables (z-scores for height-for-age [HAZ] and body mass index-for-age [BAZ]) and binary variables (prevalence of malnutrition [stunting, undernutrition, and overnutrition]), via anthropometry (Table 1). HAZ is a linear growth indicator that indicates if the child has the appropriate stature for his/her age, while BAZ is an indicator of growth that indicates if the child has the appropriate ratio of weight and height for his/her age, according to WHO guidelines [4,29,30,31,32]. We used the WHO AnthroPlus (for children 5–19 years old) software (version 3.2.2., WHO, Geneva, Switzerland) to obtain HAZ and BAZ for each child. Third we assessed handwashing prevalence via observation according to standard operating procedure (SOPs) (Figure S3).

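### Section 2.8.2 names raw weight and height where Section 2.5.1 defines HAZ and BAZ as the continuous growth outcomes, and its unadjusted weight t-test is open to age and sex confounding

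*Protocol article*

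**What the plan says.** Section 2.5.1 lists the primary outcomes. Health literacy is "measured by two continuous variables (hygiene literacy and handwashing literacy scores". Growth is measured by continuous "z-scores for height-for-age [HAZ] and body mass index-for-age [BAZ" and also by "binary variables (prevalence of malnutrition [stunting, undernutrition, and overnutrition". Observed handwashing completes the list. Raw weight and raw height are not on it.

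Section 2.8.2 introduces the comparison of arms as "using two-sided tests for primary outcomes". For continuous variables it then specifies the t-test "to calculate the mean weight differences between the control and intervention arms". The exposure-response model that follows takes the primary outcome as its dependent variable and gives the link as "identity for height and weight, logistic for stunting and poor health literacy". Literacy also appears in the risk-factor models, as "model A for poor hygiene literacy only, poor handwashing literacy only, and both poor hygiene literacy and poor handwashing literacy". The last paragraph of Section 2.8.2 assigns the question of effectiveness to generalized linear mixed models (GLMMs) but names no dependent variable. HAZ, BAZ and the literacy scores are named nowhere in Section 2.8.

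**The concern.** The article does more than leave the test variables open: it names some, and they conflict with its own outcome list. An analyst who follows Section 2.8.2 literally would test weight, which is not an outcome, and would have no named analysis for HAZ or BAZ, which are.

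The substitution matters because weight and height depend strongly on age in this range. Section 2.2 recruits grades 5 and 6 in primary schools and grades 7 and 10 in secondary schools. Section 2.5.3 places two schools in the control arm by choice, against 13 in the intervention arm. Section 2.3 takes one or two class sections per school, so two to four sections fix the age and sex mix of the whole control arm. A t-test has no covariates to absorb a difference in that mix. The note to Table 1 adds to the inconsistency: it explains that weight-for-age was passed over in favour of BAZ because weight-for-age suits only children under five. The authors thus rejected even age-standardised weight for these children.

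Two competing sets of growth variables also leave the choice of test open after the data are in. Section 2.8 plans to adjust for multiple outcomes, which presupposes a fixed list of tests.

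**Working it through.** **1. The plan's own figure.** The only design figure is N = 760 (Section 2.3). With the stated population of 2,059,447 and assumed p = 0.5, d = 0.05 and z = 1.96 (not given in the article), the Lynch formula n = N·z²·p(1−p) / (N·d² + z²·p(1−p)) gives 384.1. Then 384.1 × 1.30 × 1.45 × 1.05 = 760.2, which reproduces 760. The formula contains no effect size, SD or power for any outcome, so naming HAZ and BAZ leaves N unchanged.

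**2. The outcomes side by side.**

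| Primary outcome (2.5.1) | Named in 2.8.2 |
|---|---|
| HAZ, BAZ (continuous) | Not named; weight in the t-test, height and weight in the identity-link model |
| Two literacy scores (continuous) | Not named; poor literacy (binary) in the exposure-response and risk-factor models |
| Stunting, undernutrition, overnutrition (binary) | Matched: Poisson regression for binary variables, and model B |

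The mismatch therefore concerns the continuous outcomes only.

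**3. How far an unadjusted weight test could mislead.** The age imbalance between arms is not given, so this is an illustration. Assumptions: no effect on the age-standardised outcomes; about 50 children per school (Section 2.3), hence 2 × 50 = 100 control and 13 × 50 = 650 intervention; independent observations; two-sided 5% test; normal approximation.

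SE = SD × √(1/100 + 1/650) = SD × 0.1074. 
Rejection rate = Φ(δ/SE − 1.96) + Φ(−δ/SE − 1.96).

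*Weight at one time point.* Assumed SD 10 kg, so SE = 1.074 kg; assumed 2–5 kg per year of age, so δ = slope × gap in mean age.

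| Gap in mean age | δ (kg) | False rejections |
|---|---|---|
| 0 | 0 | 5% |
| 0.25 y | 0.5–1.25 | 7.5–21% |
| 0.5 y | 1.0–2.5 | 15–64% |
| 1 y | 2–5 | 46–99.6% |

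*Eight-month weight change.* Section 2.5.4 compares differences from baseline. That cancels differences in level but not differences in growth rate. Assumed SD of change 2–3 kg; δ = gap in annual gain × 8/12.

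| Gap in annual gain | δ (kg) | False rejections |
|---|---|---|
| 0 | 0 | 5% |
| 0.5 kg | 0.33 | 18–34% |
| 1 kg | 0.67 | 54–87% |

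With no imbalance the test keeps its 5% level. With a modest imbalance it does not, on either scale. Clustering is ignored here and is a separate matter.

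**The case against.** The strongest reply is that this is loose naming in a condensed article. The t-test sentence opens with continuous variables in general, so it could cover HAZ, BAZ and the scores. Section 2.8.1 promises arm-level results for every primary and secondary outcome. The GLMM, which is the stated efficacy model, could take any of them. Box S2 and the full models are not shown. All of that is possible, but none of it is stated. A slip of weight for weighted is also unlikely, because height and weight recur together in the regression. The reply limits the point to the named variables; it does not remove the conflict.

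Four stronger readings are tempting, and the documents do not support them.

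- *Every analysis in the section is confounded.* Height appears only in a model with a confounder vector, and the logistic models name age and sex among their confounders. The charge fits the t-test sentence.
- *Literacy is tested only as a yes/no outcome, at a cost of about a third of the sample.* Binary literacy is named in the exposure-response, risk-factor and descriptive analyses; the efficacy tests may already use the scores. A median split of a normal score would keep 2/π ≈ 64% of the information, but neither a cut-point nor a distribution is given.
- *The arms differ in age.* No grade mix by arm appears in the text. That one control school is integrated shows nothing by itself, because recruitment was limited to four grades.
- *The binary growth measures should become supportive.* Section 2.5.1 lists them as primary, and Section 2.8.2 analyses them as defined.

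**Conclusion.** The point holds for the continuous growth outcomes. Section 2.8.2 names weight for the arm comparison and height and weight for the identity-link model, where Section 2.5.1 defines HAZ and BAZ. Followed as written, the t-test would address a variable that is not an outcome and is exposed to age and sex differences between a deliberately chosen two-school control arm and the rest. Change scores do not remove that exposure.

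The size is conditional. Under the assumptions above, a half-year gap in mean age raises the false rejection rate from 5% to 15–64% for weight level, and a 0.5 kg gap in annual gain raises it to 18–34% for eight-month change. The true imbalance is unknown and could be nil. For literacy, the text only needs to say that the efficacy tests use the scores; no loss of information can be claimed. This should be settled before analysis. It does not affect the sample size or the binary outcomes.

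**What to change.** In Section 2.8.2:

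1. Replace weight in the t-test sentence, and height and weight in the link-function statement, with HAZ and BAZ. If raw weight or height is kept, analyse it in a model adjusted for age and sex, not by an unadjusted t-test.
2. State that the arm-comparison test and the GLMM take HAZ, BAZ, the hygiene literacy score and the handwashing literacy score as continuous dependent variables, as in Section 2.5.1.
3. Keep stunting, undernutrition and overnutrition as the binary primary measures they are. The poor-literacy models may remain as risk-factor or supportive analyses.

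The cost is a wording change. Section 2.5.1 already has HAZ and BAZ produced for each child and the literacy scores collected, so no new data are needed. Using z-scores removes the direct dependence on age; it does not repair the non-random choice of control schools, which Section 3 already acknowledges as a limitation.
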